### Ethical considerations

Prior to the start of the trial, protocol written approval was authorized by the local ethical committee of the Hospital of the Sisters of Charity in Linz, a member of the independent Ethics Committee (IEC) of Austria (Study number: 28/12 AirSeal™ Trial).

Following IEC approval, all subsequent protocol amendments and changes to the informed consent document must be approved by the responsible IEC. The IEC must be informed of the end of the trial. The investigator must keep a record of all communications with the IEC and the regulatory authorities.

### Patients’ confidentiality

It is the responsibility of the investigator to maintain patient confidentiality. During the trial patients will be identified solely by means of their year of birth and individual identification code (screening number plus randomization number). Trial findings will be stored in accordance with local data protection law and ICH GCP (International Conference on Harmonisation of Technical Requirements for Registration of Pharmaceuticals for Human Use provide a unified standard for the European Union, Japan, and the United States to facilitate the mutual acceptance of clinical data by the regulatory authorities in these jurisdictions) guidelines and will be handled in strictest confidence. The investigator will maintain a personal subject identification list (screening numbers with the corresponding subject name) to enable records to be identified.

### Patient protection

The responsible investigator will ensure that this study is conducted in agreement with the Declaration of Helsinki (Tokyo, Venice, Hong Kong, Somerset West and Edinburgh amendments).

## Informed consent

All patients recruited for the study will be informed of the aims of the study, collection of blood sample remains taken during routine pre- and postoperative venepuncture for immunological evaluation, the procedures and possible hazards to which he/she will be exposed and the mechanism of treatment allocation. Patients are free to withdraw from the study at any time without providing any specific reason. Furthermore, it is the responsibility of the investigator to explain to patients their duties within the trial. They will be informed about the strict confidentiality of their patient data but that their medical records may be reviewed for trial purposes by authorized individuals other than their treating physician.

### Trial insurance

This trial is comparing two standard treatments that represent current medical practice in Austria. No experimental treatment is delivered to patients within this trial. The trial is not subject to the Austrian Drug Law and may be considered as a so-called ‘free’ clinical study, for which no legal requirements exist concerning patient indemnity insurance. This trial is regulated by the Austrian Medical Device Law § 40.5. The sponsor has procured public liability insurance from the Sisters of Charity Hospital Linz that covers the conduct of clinical trials.

### Statistical considerations

From a statistical point of view the present trial shows a confirmatory status, superiority approach and a parallel group design (group A with AirSeal™ use versus group S with standard CO_2_ pressure pneumoperitoneum insufflator use). The type I error preservation by the gatekeeping approach (primary endpoint one: time of surgery (in minutes) and primary endpoint two: shoulder pain at 48 hours after end of surgery (measured using VAS)) was calculated. Stratification according to the type of surgery was done.

### Sample size estimation

On the basis of a comparison of two proportions, a sample size of 182 (n = 91 per group) is needed to have 80% power at a 5% significance level, assuming a dropout rate of 5%.

Data, assumptions and conditions are: type I error (2.5% one-sided), type II error (20%), non-parametric test (Mann–Whitney *U*-test), n (group A): n (group S) (ratio of 1:1) and per-protocol analysis:

(1)$$\begin{array}{l} \mathrm{group}\;A\;\left(\mathrm{mean}\;\pm \;\mathrm{standard}\;\mathrm{deviation}\right):\;74,8\;\pm \;41,3\;\min\\ \mathrm{group}\;S\;\left(\mathrm{mean}\;\pm \;\mathrm{standard}\;\mathrm{deviation}\right):\;93,5\;\pm \;41,3\;\min \end{array}\;\}\Delta =20\%$$

### Analysis populations

The intention-to-treat (ITT) population: all subjects in whom the use of AirSeal™ or a standard CO_2_ pressure pneumoperitoneum insufflator has already begun will be included in the ITT population. All variables will be analyzed. The ITT population will be used for the primary safety evaluation of implantation (ITT analysis).

The per-protocol (PP) population will be: all subjects without occurrence of dropout situation (all valid cases) will be included in the PP population. All variables will be analyzed. The PP population will be used for the primary efficacy evaluation (PP analysis).

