### Study population and location

The study population will consist of patients undergoing elective laparoscopic cholecystectomy, colorectal surgery and hernia repair. A clinical evaluation and pre-randomization assessment must be completed for every patient, including a review of the eligibility criteria, signed and dated informed consent, inquiry of relevant past medical history and anesthesiological preoperative assessment including American Society of Anesthesiologists (ASA) class. Dropout criteria will be if patients recruited for laparoscopic resection are converted to an open procedure. Detailed eligibility criteria are listed in Table 1.

**Table 1 T1:** Eligibility criteria

**Inclusion criteria**	**Exclusion criteria**
• Aged 18 years and over	• Previous extensive abdominal surgery
• ASA ≤ 3	• Acute surgical intervention
• Informed consent provided	• Immunological dysfunctions like advanced liver disease, HIV or hepatitis C virus infection
• Diseases of the gallbladder, colon or hernias treated with elective laparoscopic procedure	• Pregnancy and lactation

Patients who meet the eligibility criteria will be given a patient information sheet and time to consider the trial. If interested, informed consent will be obtained for each patient prior to randomization. All personal information obtained for the study will be held securely and treated as strictly confidential.

This single centre trial will be performed at a high volume institution with experience in laparoscopic surgery (Department of General and Visceral Surgery, Sisters of Charity Hospital Linz, Austria). The clinical study centre of the surgical department will conduct this trial.

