### Handling of implausible values and missing values

Implausible values have to be identified by the clinical investigator. They will be converted into missing values. Missing values will not be replaced, with the following exception: missing values at the two primary endpoints will be replaced by the mean of all plausible data (both groups) of the respective endpoint. The missing-value replacement procedure described above will be only applied to the ITT analyses (no replacement of missing values in the PP analysis).

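### The confirmatory superiority test of both primary endpoints uses a per-protocol set that leaves out patients converted to open surgery; the planned ITT analysis is not the primary one

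*Protocol article*

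**What the plan says.** Four sections of the protocol article together fix the analysis set.

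- **Statistical considerations:** "the present trial shows a confirmatory status, superiority approach and a parallel group design".
- **Study population and location:** "Dropout criteria will be if patients recruited for laparoscopic resection are converted to an open procedure". No other dropout criterion is named.
- **Analysis populations:** "all subjects without occurrence of dropout situation (all valid cases) will be included in the PP population", and "The PP population will be used for the primary efficacy evaluation (PP analysis". For the other set, "all subjects in whom the use of AirSeal™ or a standard CO_2_ pressure pneumoperitoneum insufflator has already begun will be included in the ITT population"; its stated role is that "The ITT population will be used for the primary safety evaluation of implantation (ITT analysis". Under both definitions the section adds that every variable will be analysed.
- **Sample size estimation:** per-protocol analysis is listed among the conditions behind the 182 patients.

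Two further provisions matter. Under Handling of implausible values and missing values, missing primary-endpoint values are replaced by the mean of both groups combined, and "The missing-value replacement procedure described above will be only applied to the ITT analyses (no replacement of missing values in the PP analysis". Under Statistical methods, shoulder pain is tested only if the null hypothesis for operation time has been rejected.

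**The concern.** Conversion is an intraoperative event that follows randomisation. The article's own rationale links it to the device: the Background says that good exposure affects how long an operation takes and how safe it is, and that AirSeal keeps the pneumoperitoneum stable under difficult conditions. The Discussion in the abstract expects this to influence operation time. The surgeon is not among those listed as blinded under Primary endpoints. If conversion depends on the device and on how hard the case is, removing converted patients leaves two groups that randomisation no longer makes comparable.

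The direction is not fixed. If AirSeal prevents conversions, its arm keeps difficult cases that the control arm loses, and a benefit is hidden. If AirSeal leads to more conversions, its difficult cases disappear and a benefit can appear where there is none. Because the second endpoint is gated on the first, a false rejection for operation time would also open the shoulder-pain test.

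Nothing forces the exclusion. Operation time runs from skin incision to wound closure and is routinely documented, so a converted case still has a value.

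**Working it through.** **1. The plan's own figure.** Inputs from Sample size estimation: means 74.8 and 93.5 min (difference 18.7), SD 41.3, one-sided 2.5%, power 80%, dropout 5%, stated total 182.

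n per arm = 2 × (1.960 + 0.842)² × (41.3/18.7)² = 76.6, so 77; 77/0.95 = 81.1, so 82, total 164. Allowing for the Mann–Whitney test gives 172 to 174 (efficiency 3/π) or 176 (Noether formula). The stated 182 is not reproduced exactly but lies above all of these. The mismatch does not bear on this point.

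**2. Power if every operated patient is kept.** Power = Φ(18.7 / (41.3 × √(2/n)) − 1.960).

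- n = 91: 18.7/6.12 = 3.05, power 86.3%; with efficiency 3/π (effective n 86.9), 84.7%.
- n = 86 (about 5% lost): 84.4% and 82.7%.

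On these inputs no larger sample is needed, provided converted cases neither dilute the difference nor raise the SD.

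**3. How far a few exclusions move a mean.** Assume that 5 of 91 patients in one arm convert, each with a time of 180 min. The other 86 have mean (91 × 93.5 − 5 × 180)/86 = 88.5 min, a shift of 5.0 min. The planned difference is 18.7 min.

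**4. Error rate, illustration only.** The conversion rates and the link to operation length are assumptions; the documents give neither. All runs have 91 per arm, no true effect and a one-sided 2.5% Mann–Whitney test.

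- Model 1: one gamma distribution (mean 93.5, SD 41.3), conversions drawn from the longer half of operations, 4000 trials.
- Model 2: mix of 46/27/18 patients with means 75/83/155.5 and SDs 24/25/38 (overall mean 8490/91 = 93.3), same mix in both arms, conversion probability proportional to the fourth power of the rank of operation time, 2000 to 3000 trials.
- Model 3: as model 2, with the mix left to vary by chance.

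| Conversions A / S | Model 1 | Model 2 | Model 3 |
|---|---|---|---|
| 5% / 5% | 2.3% | 1.1% | not run |
| 6% / 4% | not run | 1.4% | not run |
| 8% / 2% | 5.3% | 3.4–4.3% | 8.1% |
| 10% / 0% | 9.0% | 7.7–9.5% | 13.0% |
| 2% / 8% | 1.0% | not run | not run |
| All patients kept | 2.3–2.7% | 0.3–0.6% | 2.5–2.8% |

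At 8%/2% the spurious advantage for AirSeal is 2.1 min in model 1 and 3.5 min in model 2.

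Model 2 with a weaker link (conversion proportional to rank) gives 1.4% at 8%/2% and 1.5% at 10%/0%. Model 2 needs care: an unstratified test on arms with an identical procedure mix is conservative, which is why its all-patient rate is so low. The fair yardstick is the nominal 2.5%. For the same reason the 1.4% shows that the size depends on the steepness of the link; it does not show that a weak link is harmless in every model.

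**5. Effect on the estimate.** In model 1 with a true difference of 18.7 min, the per-protocol estimate is 20.7 min at 8%/2% and 16.8 min at 2%/8%. In model 2 with conversions of 0% (A) and 10% (S), each adding 30 min, per-protocol shows AirSeal slower by 6.0 min when across all patients it is faster by 2.9 min.

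**The case against.** **ITT efficacy is already planned.** A reader might infer from the safety role given to the ITT set that no ITT analysis of efficacy exists. The documents do not support that. All variables are to be analysed in ITT, and the replacement rule for the two primary endpoints applies only there. The ITT set, patients in whom device use has begun, is also close to the set recommended here. This objection stands: the defect is which of two planned analyses is primary. It does not remove the point, because the confirmatory decision and the gate still rest on per-protocol, and pooled-mean replacement makes the ITT analysis an imperfect fallback.

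**The numbers rest on strong assumptions.** This also stands. Error clearly above nominal needed an uneven split and conversion tied to long operations. That tie is an inference; the documents do not state it.

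**The claimed mechanism points the other way.** Better exposure suggests fewer conversions with AirSeal, and per-protocol is then conservative (1.0% at 2%/8%). A reader might conclude that the plan favours the device. The documents support no direction. Conservative bias is still bias, and it costs power.

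**Scope of the criterion.** It speaks of patients recruited for laparoscopic resection, so its coverage of all three procedures, hernia repair in particular, is unclear. That affects how many patients are excluded, not the principle.

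**Wording.** The reference to implantation is an editorial slip. The per-protocol condition in the sample-size section agrees with the analysis-set section, so there is no contradiction between them.

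**Conclusion.** The point holds in this form: a trial declared confirmatory for superiority bases its primary efficacy evaluation on a set selected by an intraoperative event that the device may influence, while the planned ITT analysis of the same endpoints is not the confirmatory one.

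The size cannot be derived from the documents. Under assumed conversions of 8% against 2% and a strong link to long operations, the one-sided error is about 4 to 5% instead of 2.5% in the first two models, with 8.1% in the third. It was at or below nominal with equal rates, and with a weak link in the model where that was tried. It falls below nominal if AirSeal prevents conversions, at the price of an understated benefit. These figures show that the result can depend on conversion; they do not predict a false positive.

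**What to change.** 1. Under Analysis populations, make the primary efficacy analysis of both primary endpoints that of all randomised patients who undergo the operation, by assigned arm.
2. Use the actual incision-to-closure time and recorded shoulder-pain VAS of converted patients. Observed values should not be treated as missing, so that the pooled-mean replacement is not applied to them.
3. Keep the per-protocol analysis as a sensitivity analysis, and state which procedures the conversion criterion covers.
4. Report conversions by arm.
5. Align the per-protocol condition under Sample size estimation.

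The cost is wording, since operation time is already documented. The downside is some extra variance from long converted cases. At most, the analysed number rises from about 86 to 91 per arm (0.95 × 91 = 86.5); that assumes all of the 5% dropout is conversion, and patients who withdraw would not be recovered. The change should be made before the data are analysed.

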### Handling of implausible values and missing values

Implausible values have to be identified by the clinical investigator. They will be converted into missing values. Missing values will not be replaced, with the following exception: missing values at the two primary endpoints will be replaced by the mean of all plausible data (both groups) of the respective endpoint. The missing-value replacement procedure described above will be only applied to the ITT analyses (no replacement of missing values in the PP analysis).

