### Primary endpoints

Operation time, defined as the time from skin incision to closure of wound in minutes, is routinely documented in our operation program and will be evaluated after the operation by a newly designed survey. Postoperative shoulder pain will be assessed within 48 hours after the operation using the visual analogue pain scale (VAS). Postoperative pain will be assessed in a double-blinded manner, neither the patient, the assessor of shoulder pain, nor the postoperative caregivers will be aware of the technique to which the patient will been randomized.

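### Values judged implausible are set straight to missing, with no verification step and no statement that the judgement is masked to arm; operation time, the gatekeeping endpoint, is the one exposed

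*Protocol article*

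**What the plan says.** The section on handling of implausible and missing values sets the rule: "Implausible values have to be identified by the clinical investigator. They will be converted into missing values". The same section then applies it to the primary endpoints. In the ITT analysis, "missing values at the two primary endpoints will be replaced by the mean of all plausible data (both groups) of the respective endpoint"; for the per-protocol analysis it specifies "no replacement of missing values in the PP analysis". Under Analysis populations, "The PP population will be used for the primary efficacy evaluation (PP analysis").

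Under Primary endpoints, operation time "is routinely documented in our operation program" and "will be evaluated after the operation by a newly designed survey". The masking described there concerns postoperative pain: the patient, the shoulder-pain assessor and the postoperative caregivers do not know the technique. The section is silent on masking for operation time.

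Under Data collection, the clinical investigator makes the daily visits at which outcome information is gathered. Under Statistical methods, shoulder pain is tested only if the operation-time hypothesis is rejected. That hypothesis is tested with an exact Mann-Whitney test at 2.5% one-sided.

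**The concern.** The article states a rule here; it is not simply leaving a detail to the analysis plan. The prescribed consequence of an implausibility judgement is deletion, although for operation time the article itself names a routine record against which a doubtful value could be checked.

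Three features make operation time the exposed endpoint. No masking is stated for it. The primary efficacy analysis is per-protocol without replacement, so a struck time drops out of the confirmatory test. The population mixes short and long procedures, so genuine long times will occur, and the rule as written does not separate a long but true time from a recording error.

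If judgements differed by arm, the test that opens the gate to endpoint two would be biased. Long times struck mainly from group A would favour AirSeal; struck mainly from group S, the reverse.

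**Working it through.** **1. Inputs from the article (Sample size estimation).** Means are 74.8 min (group A) and 93.5 min (group S), with SD 41.3 in both. The difference is 93.5 − 74.8 = 18.7 min, and 18.7/93.5 = 20%, which matches the stated effect. There are 91 patients per group; after 5% dropout, 91 × 0.95 = 86.45, so about 86 are evaluable.

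**2. Assumed distribution.** The article gives no distribution by procedure. Assumed for one arm: lognormal times in strata of 46, 27 and 18 patients, with means 75, 83 and 155.5 min and SDs 24, 25 and 38.
- Mean: (46×75 + 27×83 + 18×155.5)/91 = 8490/91 = 93.3 min.
- Within-stratum variance: (46×24² + 27×25² + 18×38²)/91 = 69363/91 = 762.
- Between-stratum variance: about 966.
- SD: √(762 + 966) = 41.6 min.

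Both figures are close to the plan's 93.5 and 41.3.

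**3. Scenario.** No true difference; the k longest times are removed from group A only. This is the worst case for a false claim in favour of AirSeal.

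**4. Size on the scale of the planned test.** The planned test is rank-based, so the matching effect estimate is the Hodges-Lehmann shift (the median of all between-group pairwise differences).

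| k removed | Hodges-Lehmann shift | Share of 18.7 min |
|---|---|---|
| 2 | about 1.3 min | 7% |
| 3 | about 1.7 min | 9% |
| 5 | about 2.8 min | 15% |

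Repeat runs agree to within about 0.3 min.

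**5. One-sided Mann-Whitney error, nominal 2.5% (asymptotic p-values).**

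| k removed | Procedures exactly balanced | Mix varies by chance |
|---|---|---|
| 0 | 0.3% | near nominal |
| 3 | 1.6% | 5.8% |
| 5 | 3.8% | 9.9% |

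Repeat runs of the balanced case gave up to 2.4% (k = 3) and 4.6% (k = 5). With 4,000 runs the standard error near 2% is √(0.02×0.98/4000) = 0.2 percentage points, so the balanced figures are good only to roughly half a point. The balanced case starts far below 2.5% because the unstratified test counts between-procedure spread as noise even though the arms are matched on it.

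**6. Simpler model and the ITT analysis.** A single lognormal with mean 93.5 and SD 41.3, 86 per arm and 20,000 runs gives 2.4% with no removal. Per-protocol error is then 6.3% (k = 3) and 9.9% (k = 5). With pooled-mean replacement, as in the ITT analysis, it is 5.7% and 8.2%. Replacement softens the effect but does not remove it.

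**7. Effect of masking.** In the same single-lognormal model, removing the k longest times without regard to arm gives 2.7% (k = 3), 2.5% (k = 5) and 2.4% (k = 8). The problem lies in removal that differs by arm, not in removal as such.

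**The case against.** A reader might infer that the judgement is made by someone who knows the arm. The article does not say so. The clinical investigator makes the daily visits, shoulder pain is recorded at those visits, and the pain assessor is masked; the person judging plausibility may therefore be masked. Nor does the article say that the survey records the insufflator: it names blood gas and ventilation data. The supportable statement is that masking of this decision is not stated for operation time. For shoulder pain the concern is weaker, because assessment is masked.

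A reader might also infer that values are never checked. Query procedures and plausibility limits commonly sit in a data management or analysis plan that is not shown, and identifying a value as implausible does not exclude looking at the record first. That stands as far as it goes, but the rule that is printed leads from implausible to missing with no branch for correcting or confirming the value.

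Third, a reader might size the problem by the mean. The same removals shift the mean difference by 2.9, 4.1 and 6.3 min, or 16%, 22% and 34% of 18.7 min. That overstates it, because the planned test uses ranks and the corresponding shifts are less than half as large.

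Finally, the scenario is adversarial. In the assumed mixture the five longest times average roughly 179 to 236 min, against an assumed colorectal mean of 155.5 min. An investigator would have to call fairly ordinary colorectal durations implausible, and in one arm only. The article expects long colorectal times and chooses its test because of them. This objection stands, and it is why the point concerns opportunity only.

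**Conclusion.** The point holds in limited form. The article fixes deletion as the consequence of an implausibility judgement on the primary endpoints, without stating verification, correction or masking to arm, and the deleted value then affects the gatekeeping analysis. No bias is demonstrated.

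Even the worst case with five removals moves the rank-based estimate by about 15% of the planned effect. Whether the 2.5% level is exceeded depends on the model: with procedures exactly balanced it is not exceeded at three removals but is at five; with a mix that varies by chance it is exceeded at both. Stratified randomisation should place the trial nearer the balanced case, though the article does not establish exact balance.

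These figures rest on the assumed mixture, the assumed number of removals and removal from group A only. Severity is minor to moderate: the likely effect is small, but a trial that calls itself confirmatory can close the gap at almost no cost.

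**What to change.** Replace the deletion rule with the following:
- Implausible values are flagged on listings without treatment arm, before database lock.
- Each flagged value is checked against the source record; for operation time this is the operation program.
- A value shown to be wrong is corrected, and a value confirmed by the source is kept.
- A value is set to missing only when a recording error is shown and no source value exists.

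Name the operation-program time as the source for primary endpoint one, since the present text leaves its relation to the survey unclear. Add a sensitivity analysis of operation time with all recorded values kept, and report the number of values changed or set to missing by arm.

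The cost is a change of wording and a short masked listing review. No new data are needed for operation time, which the article says is already documented routinely.

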### Statistical methods

The estimation of effect size for selected variables will be the calculation of two-sided 95% confidence intervals.

Primary endpoint one will be set due to the clear duration difference between colorectal surgery and the other types of surgery (laparoscopic cholecystectomy and laparoscopic hernia repair) a normal distribution of the data can be excluded. Therefore, a nonparametric test, namely the exact Mann–Whitney *U*-test will be used (type I error = 2.5% one-sided).

Primary endpoint two (only if H0_PE1_ is rejected), will be set by checking data sets for normal distribution (test of normality: Kolmogorov-Smirnov with Lilliefors significance correction, type I error = 5%). In the case of normal distribution the *t*-test for independent samples with correction for heteroscedasticity (Levene’s test, type I error = 5%) will be applied. In the case of a significant deviation from the normal distribution the exact Mann–Whitney *U* test will be used instead. In both cases the type I error will be 2.5% one sided.

Metric variables data sets will be checked for normal distribution (test of normality: Kolmogorov-Smirnov with Lilliefors significance correction, type I error = 5%). Normally distributed data sets will be compared between the groups by the *t*-test for independent samples with correction for heteroscedasticity (Levene’s test, type I error = 5%). If there is a significant deviation from the normal distribution the exact Mann–Whitney *U* test will be used instead.

Ordinal variables will be checked by the exact Mann–Whitney *U* test and nominal variables by the exact chi-square homogeneity test or, for 2 × 2 frequency tables the Fisher's exact test.

All tests will be two-sided with a confidence level of 95% (*P* <0.05). As no adjustment of the *P* values will be made, the resulting *P* values will only be descriptive.

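### In the ITT analyses, every missing primary-endpoint value is filled with one mean pooled over both arms and all procedures, so they are a poor check on the per-protocol result

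*Protocol article*

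**What the plan says.** Under *Handling of implausible values and missing values*, the general rule is no replacement, with one exception: "missing values at the two primary endpoints will be replaced by the mean of all plausible data (both groups) of the respective endpoint". No stratum is named, so all three types of operation share the same mean. The same section adds to the missing values: "Implausible values have to be identified by the clinical investigator. They will be converted into missing values". It then limits the scope: the procedure "will be only applied to the ITT analyses (no replacement of missing values in the PP analysis").

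Under *Analysis populations*, "The PP population will be used for the primary efficacy evaluation (PP analysis"), while "The ITT population will be used for the primary safety evaluation of implantation (ITT analysis"). All variables are nevertheless to be analysed in both populations. Under *Study population and location*, "Dropout criteria will be if patients recruited for laparoscopic resection are converted to an open procedure". Converted patients therefore leave the PP population and remain only in the ITT population.

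Under *Statistical methods*, a rank test is chosen for operation time "due to the clear duration difference between colorectal surgery and the other types of surgery", and randomization is stratified by type of operation.

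**The concern.** The rule puts one number in place of every missing value, whichever arm the patient was in and whichever operation was done. That sits badly with the article's own reasoning. It sets normality aside because procedures differ in duration, and then gives a colorectal, a gallbladder and a hernia patient the same filled-in time. A value removed as implausibly extreme re-enters the ITT analysis as an average one.

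Three consequences follow within the ITT analyses. The mean difference is diluted. The spread is understated, because invented values count as observed. And where the mean lies above the median, each filled-in patient ranks worse than most observed patients, so unequal missingness alone can move a rank test.

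At stake is the value of the ITT result as a check. It is the only analysis that keeps converted patients, so a reader will look to it to see whether the PP result depends on excluding them.

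**Working it through.** **Planning figures.** *Sample size estimation* gives 74.8 ± 41.3 min (A) and 93.5 ± 41.3 min (S). The difference is 93.5 − 74.8 = 18.7 min, and 18.7/93.5 = 20%, as stated. The normal formula gives 2 × (1.960 + 0.842)² × (41.3/18.7)² = 76.6, so 77 per group (78 with the *t* distribution). An allowance of 10% for the rank test (my assumption, not stated) gives 86, and 86/0.95 = 90.5, so 91 per group or 182 in all. The planning inputs can therefore be used below. The pooled mean on them is (74.8 + 93.5)/2 = 84.2 min.

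**Step 1: dilution of the mean difference.** With a fraction m missing at random in each arm, each arm's mean becomes (1 − m) × own mean + m × pooled mean. The difference is therefore (1 − m) × 18.7:
- m = 5%: 0.95 × 18.7 = 17.8 min (simulated 17.6–17.8)
- m = 10%: 0.90 × 18.7 = 16.8 min (simulated 16.7–16.9)
- 10% in S only: pooled mean (74.8 + 0.9 × 93.5)/1.9 = 83.7; S becomes 0.9 × 93.5 + 0.1 × 83.7 = 92.5; difference 17.7 min

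**Step 2: variance.** With m = 5% per arm, the filled-in SD is √(0.95 × 41.3² + 0.95 × 0.05 × 9.35²) = 40.3 min, where 9.35 is half of 18.7. The apparent standard error of the difference is 40.3 × √(2/91) = 6.0 min. Observed values alone give 41.3 × √(2/(0.95 × 91)) = 6.3 min, and complete data 41.3 × √(2/91) = 6.1 min. The filled-in data thus look more precise than a trial with nothing missing.

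**Step 3: ranks under no true effect.** Simulation: 91 per arm, values missing at random, pooled-mean fill, one-sided 2.5% Mann–Whitney test (asymptotic p), 20,000 replicates. The level and the test come from the article ("type I error (2.5% one-sided), type II error (20%), non-parametric test (Mann–Whitney *U*-test")). The shapes and missing rates are assumptions, because the article gives neither:
- normal and lognormal: mean 93.5, SD 41.3
- mixture: 25% long operations (150 ± 25 min) and 75% short (74.67 ± 20 min), so the mean is 0.25 × 150 + 0.75 × 74.67 = 93.5
- VAS: 60% zeros, the rest a rounded gamma between 1 and 10

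The pooled mean lies at the 58th percentile (lognormal) and the 62nd (mixture). In the mixture it is 150 − 93.5 = 56.5 min below the mean of a long operation.

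One-sided rejection in favour of A (%):

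| Shape | None missing | 5% in each | 5% in S only | 10% in S only | 10% in A only |
|---|---|---|---|---|---|
| Normal | 2.6 | 2.6 | 2.3 | 2.4 | 2.6 |
| Lognormal | 2.5 | 2.4 | 3.1 | 3.9 | 1.4 |
| Mixture | 2.6 | 2.4 | 3.4 | 4.4 | 1.1 |
| VAS | 2.5 | 2.3 | 4.8 | 7.2 | 0.6 |

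With 10% missing in one arm only, using observed values alone kept the error near 2.5% (2.0–2.9% for the three operation-time shapes, at 3,000 replicates).

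**Step 4: limits.** In the mixture with the planned effect and 10% missing in S only, P(A<S) was 0.660 with the fill and 0.655 without, and rejection was 0.965 against 0.947. With no effect but the missing values drawn from the longest quarter of operations (10% of A only), P(A<S) was 0.528 and rejection 0.095. Leaving those patients out was worse (0.541 and 0.154).

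**Step 5: PP analysis.** No value is replaced there, so the rule has no effect on it.

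**The case against.** The strongest reply is that the primary efficacy result does not depend on this rule. That stands. A reader might infer that the confirmatory test is biased, but replacement is confined to the ITT analyses and both the efficacy evaluation and the sample size rest on the PP population.

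A reader might also infer that the rule always pulls the effect towards zero, or always works against the arm with more missing data. Step 4 shows neither is general. Dilution holds for mean differences, but the rank effect can move away from zero. The rank shift needs skew and missingness unrelated to the value, vanishes with symmetric data, and reverses if long operations are missing.

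The sizes rest on assumptions. The only related figure in the article is 5% dropout, and dropout is defined as conversion, not as a missing endpoint. Blinded pain assessment at daily visits gives no obvious reason for strong imbalance in VAS. Against that, one section sets the pain endpoint at 48 hours and Table 2 marks shoulder VAS only for daily ward visits, so a patient discharged earlier may have no 48-hour value.

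Operation time is routinely documented, so few values should be missing. Shoulder pain is tested only if operation time succeeds, so the VAS percentages describe that test alone, not the trial's overall error rate. With equal missingness the loss of power is also small (at 10% per arm, 0.794 against 0.803 for normal data and 0.918 against 0.930 for the mixture).

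These points limit the size and reach of the problem. None gives a reason to prefer a pooled mean.

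**Conclusion.** The concern holds for the ITT analyses of the two primary endpoints and for nothing else. There the fill ignores arm and the stratification factor, shortens the mean difference by about the missing fraction and makes the data look more precise than they are. These effects follow from the rule itself when values are missing at random.

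The shift in the one-sided Mann–Whitney error is conditional: roughly 3–7% with 5–10% missing in S only, and roughly 1% with 10% missing in A only, for the assumed skewed or zero-heavy shapes. A wider imbalance would move it further; equal missingness or symmetry largely removes it. The sign cannot be known in advance, and that is what makes the ITT analysis a poor check on the PP result. The rule should be changed, but it does not undermine the planned primary efficacy analysis. Whether ITT ought to be primary is a separate question on which this point does not rely.

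**What to change.** Delete the pooled-mean rule.

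- **Operation time:** take a missing value from the routinely documented operation program and do not impute it. This also avoids the bias that arises when long operations are simply left out.
- **Shoulder VAS:** analyse the observed values in the ITT population with the planned test. Add multiple imputation conditional on arm, type of operation, the patient's other VAS ratings and baseline data already collected (age, sex, BMI, ASA).
- **Pooling:** apply Rubin's rules to an estimate with a standard error, such as a mean difference or the Mann–Whitney probability. They do not directly combine exact Mann–Whitney p-values.

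The cost is a change of wording and slightly more programming. No further patients or measurements are needed.
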